#### 8.2.3.7 *Urinalysis with Microscopic Analysis*

Urinalysis with microscopic analysis will be performed at screening, pre-treatment, Days 6, 14, 30, and 42. The test should include measurements of urinary protein, glucose, ketones, hemoglobin, bilirubin, pH, specific gravity, red cell count, white cell count, epithelial cells, casts, and crystals. The screening urinalysis must be performed within 7 days prior to infusion of I-131-CLR1404.

#### 8.2.3.8 *Hematology*

Blood will be drawn for hematology measurements at screening, pre-treatment, Days 6, 14, 30 and 42. The following testing should be performed at each time point: CBC with RBC, MCV, MCH, MCHC; hemoglobin, hematocrit, WBC count (with differential % neutrophils, lymphocytes, monocytes, eosinophils, basophils,) absolute neutrophil count, and platelet count. Screening labs must be drawn within 7 days prior to infusion of I-131-CLR1404.

#### 8.2.3.9 *Chemistry*

Blood will be drawn for evaluating chemistry values at screening, pre-treatment, Days 6, 14, 30 and 42. The following labs should be performed: Sodium, potassium, total protein, bicarbonate, chloride, BUN, GGT, creatinine, glucose, calcium, SGOT, SGPT, alkaline phosphatase, total bilirubin, and albumin.

#### 8.2.3.10 *Lipids*

Blood will be drawn for evaluating serum lipids pre-treatment, and 72 hours post infusion. The following labs should be performed (fasting): total cholesterol, HDL, LDL and triglycerides.

#### 8.2.3.11 *Pharmacokinetic Analysis*

Blood will be drawn for plasma PK analysis at pre-treatment, 5, 15, 30, and 60 minutes post infusion, at each imaging visit, and on Days 14, 30 and 42. Blood samples for plasma PK analysis will be collected into EDTA (lavender top) anticoagulation tubes at each time point. Samples should be centrifuged and plasma collected, equally divided into two separate aliquots, and placed in 2 ml cryovials. Shipping materials will be provided for frozen shipment to Collectar. For detailed instructions on handling PK samples refer to the Covance laboratory manual and the Laboratory and Biodistribution Manual.

#### 8.2.3.12 *Biodistribution Analysis*

Blood will be drawn for radiologic biodistribution analysis at pre-treatment, 5, 15, 30, and 60 minutes post infusion, at each imaging visit, and on Days 30, and 42. Samples for biodistribution analysis will be collected into EDTA (lavender top) anticoagulation tubes at each time point. Duplicate aliquots of anticoagulated whole blood will be removed from the sample for analysis. Measured aliquots of whole blood samples will be counted in a well counter in the nuclear medicine department (or designated area) and compared with a known standard of I-131. For detailed instructions on handling biodistribution samples refer to the Laboratory and Biodistribution Manual.

#### 8.2.3.13 *Total Urine Collection for Radiologic Analysis*

The patient will be instructed to collect 100% of their urine for the first 14 days of the study. If after analysis of the Day 6 urine sample there is no measureable radioactivity in the urine, the patient may be instructed to discontinue further urine collection at that time point. The urine collection will begin at the first void after the 15-35 minute post infusion scan. Urine will be collected in the following incremental time points: 0-24 hours, 25-48 hours, 49-72 hours, 73-96 hours, Days 4-6, Days 6-10, and Days 10-14. Patients will be given containers in which to collect and store their urine, and instructions on how to accomplish the task successfully with minimal spillage. The urine will be brought to the nuclear medicine department (or designated area) for processing. The nuclear medicine research technologist or designee will measure the total volume for each time period, draw duplicate aliquots from each volume, and count representative samples in the well counter in comparison with a known standard of I-131. For detailed instructions on handling biodistribution samples refer to the Laboratory and Biodistribution Manual.

#### 8.2.3.14 *Whole Body Imaging*

Planar whole body nuclear medicine scans will be obtained of the patient, from the anterior and posterior projection, at the following times post injection: 15 – 35 minutes, 4-6 hours, 18-24 hours,  $48 \pm 6$  hours,  $72 \pm 6$  hours,  $144 \pm 6$  hours, and  $14 \pm 1$  Days. These images will be acquired with a high energy parallel hole collimator, on a triple energy window with a 20% symmetric peak, at a minimum of 256 x 1024 matrix, and for a speed of no faster than 10 cm/min. With the exception of the scan acquired 15 minutes post injection, the patient should void their bladder prior to each imaging session. For details regarding patient positioning, camera quality control, and image acquisition, refer to **Appendix D: Whole Body Scanning and Dosimetry** as well as the Nuclear Medicine and Radiopharmacy Manual.

#### 8.2.3.15 *Optional SPECT Imaging*

At the Investigator's discretion, SPECT imaging may be obtained between Days 3 and 14 to further characterize the patient's tumor(s).

### 9. ADVERSE EVENT REPORTING

#### 9.1 DEFINITIONS

##### 9.1.1 Adverse Event

An *adverse event* (AE) is any untoward medical occurrence in a patient or clinical investigation subject administered a medicinal product. The adverse event does not necessarily have to have a causal relationship with this treatment. An adverse event can therefore be any unfavorable and unintended sign (including an abnormal laboratory finding, for example), symptom, or disease temporally associated with the use of a medicinal product, whether or not considered related to the medicinal product.

Baseline signs and symptoms will be recorded. All adverse events that occur (whether treatment related or not) will be recorded at each visit for the duration of the study. Adverse events occurring after the signing of the informed consent but prior to the first infusion of I-131-CLR1404 will be recorded in the medical history section of the case report form (CRF). Any worsening of a baseline condition, in frequency or severity, will be recorded as an AE.

An untoward medical event which occurs outside the period of follow-up as defined in the protocol will not be considered an adverse event. Worsening of a medical condition for which the efficacy of the study drug is being evaluated will not be considered an adverse event.

Investigators should follow patients with adverse events until one of the following occurs:

- The event has subsided or disappeared.
- The condition has stabilized.
- The event is resolved.
- The patient is lost to follow up.
- 42 days have passed since the infusion of the study drug. (Adverse events which are deemed to be related to the study drug will be followed until the event has resolved, even if the event lasts longer than the 42 days of study duration).

#### 9.1.2 Unexpected Adverse Event

An *unexpected adverse event* is one for which the nature or severity of the event is not consistent with the applicable product information, e.g., the Investigator's brochure.

#### 9.1.3 Serious Adverse Event

A *serious adverse event* (SAE) is any untoward medical occurrence that at any dose:

- Results in death
- Is life-threatening (an event in which the patient was at risk of death at the time of the event; it does not refer to an event which hypothetically might have caused death if it were more severe)
- Requires in-patient hospitalization or prolongation of existing hospitalization
- Results in persistent or significant disability/incapacity
- Is a congenital anomaly or birth defect
- Other important medical events that may not be immediately life-threatening or result in death or hospitalization but may jeopardize the patient or may require intervention to prevent one of the other outcomes listed above. Examples of such events are intensive treatment in an emergency room for allergic bronchospasm; blood dyscrasias or convulsions that do not result in hospitalization; or development of drug dependency or drug abuse.

The term “severe” is often used to describe the intensity (severity) of an event. The event itself may be of relatively minor medical significance (such as a severe headache). This is not the same as “serious”, which is based on patient/event outcome - a criterion usually associated with events that pose a threat to a patient’s life or functioning.

## *9.2 EXPEDITED REPORTING OF ADVERSE EVENTS*

All fatal or life-threatening adverse events must be reported to Collectar Medical Monitor immediately by telephone or e-mail. Within 24 hours of first knowledge of the event, the SAE form must be faxed to the Medical Monitor whether full information regarding the event is known or not. If full information is not known, additional follow-up by the Investigator will be required.

All other SAEs must be reported to Collectar Medical Monitor within 24 hours by phone, e-mail or fax. Within 24 hours of first knowledge of the event, the SAE form must be faxed to the Medical Monitor whether full information regarding the event is known or not. If full information is not known, additional follow-up by the Investigator will be required.

Follow-up reports must be sent to the Medical Monitor within 48 hours of first knowledge of follow-up information on SAEs.

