### 6.2 RECRUITMENT METHODS

The methods used for recruitment of patients in the study will be devoid of any procedures that may be construed as coercive. The recruitment process will not involve any restrictions on sociodemographic factors including gender or ethnic characteristics of the patient population. However, the composition of the study patient population will depend on patient sources available to the clinical site.

Patients will be recruited through an existing database of oncology patients, clinic contacts, and referring physicians. Anticipated recruitment rate is approximately four patients per month.

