### *10.2 DOSE LIMITING CRITERIA*

In general, Dose Limiting Toxicities (DLTs) will be considered as toxicities that are related to treatment with I-131-CLR1404 and that are:

1. Hematological
  - a. Any CTCAE Grade 4 toxicity (except Grade 4 neutropenia without concurrent fever which must be present for  $\geq 7$  days to constitute a DLT)
  - b. CTCAE Grade 3 neutropenia with fever
  - c. CTCAE Grade 3 thrombocytopenia associated with bleeding
2. Non-Hematological
  - a. Any CTCAE Grade 3 toxicity despite adequate supportive care (supportive care limited to nausea, vomiting and diarrhea only)
  - b. Any CTCAE Grade 4 toxicity

If 2 patients experience a DLT, study enrollment will be stopped pending discussions with the Principal Investigator, Collectar Medical Monitor and the Agency.

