#### *11.2 DATA QUALITY ASSURANCE*

Case report forms will be checked for correctness against source document data by Collectar's monitors. If any entries on the CRFs are incorrect, incomplete or illegible, the monitor will ask the Investigator or the study clinical site staff to make appropriate corrections. Once the CRF page is complete, it will be delivered to Collectar for entry into an electronic database. Prior to this, the completed CRF will again be reviewed for completeness, consistency and legibility. Any discrepancies will be noted on a data clarification form (DCF) which will be sent to the clinical site. The discrepancy will be clarified on the DCF, which will then be returned to Collectar's data entry center.

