#### *12.4 MONITORING*

A clinical monitor will make regularly scheduled trips to the clinical site to review the progress of the study. The actual frequency of monitoring trips will depend on the enrollment rate and performance at each clinical site. At each visit, the monitor will review various aspects of the study including, but not limited to, screening and enrollment logs, compliance with the protocol and with the principles of ICH GCP, completion of case report forms, source data verification, study drug accountability, and storage, facilities and staff.

During scheduled monitoring visits, the Investigator and the clinical site staff must be available to meet with the study monitor in order to discuss the progress of the study, make necessary corrections to case report form entries, respond to data clarification requests and respond to any other study-related inquiries of the monitor.

In addition to the above, a representative from Collectar's auditing staff or government inspectors may review the conduct/results of the study at the clinical site. The Investigator must promptly notify Collectar of any audit requests by regulatory authorities.

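### The two-DLT enrolment stop can act late, because a related, non-serious Grade 3 non-haematological DLT has no reporting deadline to the sponsor

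*Protocol*

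**What the plan says.** **Stopping rule (Protocol 10.2).** "If 2 patients experience a DLT, study enrollment will be stopped pending discussions with the Principal Investigator", the Medical Monitor and the regulator. The count is study-wide: up to nine patients (6.1) at about four sites (5.2). It is the only numeric safety stop in the protocol.

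**What counts as a DLT (10.2).** The event must be related to treatment and meet a CTCAE grade criterion. Limb 2a, for non-haematological events, reads "Any CTCAE Grade 3 toxicity despite adequate supportive care", with the supportive-care proviso confined to nausea, vomiting and diarrhoea. Seriousness plays no part.

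**What must be reported quickly (9.2).** Fatal or life-threatening events go to the Medical Monitor immediately. Beyond those, "All other SAEs must be reported to Collectar Medical Monitor within 24 hours by phone, e-mail or fax". Section 9.1.3 states that severity and seriousness are different things.

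**What happens to other events.** Section 9.3 sends every adverse event to the source documents and the CRF. The CRF is handwritten (11.1) and checked by monitors, and then "Once the CRF page is complete, it will be delivered to Collectar for entry into an electronic database" (11.2). No transfer deadline is given. Under 12.4, "The actual frequency of monitoring trips will depend on the enrollment rate and performance at each clinical site".

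**Other notices.** Section 10.1 asks for timely notice of withdrawals, without a deadline, and makes removal after a DLT optional.

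**The concern.** The stop depends on a count that no single site can be relied on to hold, and one class of countable event has no timed route to the person who could hold it. An outpatient Grade 3 laboratory abnormality judged related to the drug is an example. It can satisfy limb 2a without meeting any SAE criterion, and an investigator who follows the protocol exactly may simply enter it on the CRF.

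Three features make this matter:
- Only one infusion is given, so a patient with a DLT has no dosing to stop and can stay in follow-up. The withdrawal notice may then never be triggered.
- Nobody is assigned the cross-site count. Section 10.2 brings in the Medical Monitor only for the discussions after the count is reached.
- Section 9.2 promises notice to other investigators only when regulatory expedited-reporting criteria are met, so one site need not hear of another's DLT.

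At stake is further infusion of an agent about which section 11.3 says little is known, after the protocol's own stopping condition has been met.

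**Working it through.** The protocol gives no figure for how quickly the rule should act, so there is none to reproduce.

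**Step 1: which DLTs have a deadline**

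| 10.2 limb | Route to the sponsor |
|---|---|
| 1a, 2b: Grade 4 | 9.4.1 equates Grade 4 with life-threatening, and 9.2 then requires immediate report |
| 1b, 1c: Grade 3 neutropenia with fever, Grade 3 thrombocytopenia with bleeding | Mostly reachable through the blood-dyscrasia example in 9.1.3, then 24 hours |
| 2a: Grade 3 non-haematological, serious | 24 hours |
| 2a: Grade 3 non-haematological, not serious | No deadline |

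The gap is the last row.

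**Step 2: illustration of the delay**

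Inputs:
- Accrual: "Anticipated recruitment rate is approximately four patients per month" (6.2), read as study-wide. With 30.4 days per month, infusions are 30.4/4 = 7.6 days apart, and the ninth falls on day 8 × 7.6 = 60.8.
- Detection day t: 6, 14, 30 or 42. These are the scheduled haematology and chemistry days after infusion (8.2.3.8, 8.2.3.9).
- Reporting lag L: 1 day for 24-hour reporting. For the CRF route the protocol states none, so 7, 14, 28 and 42 days are assumed.
- Patients 1 and 2 have the DLTs (assumed).

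The second DLT is known on study day T = 7.6 + t + L. Patients infused by then = min(9, floor(T/7.6) + 1).

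For t = 14:
- L = 1: T = 22.6; 22.6/7.6 = 2.97, so 3 of 9
- L = 7: T = 28.6; 3.76, so 4 of 9
- L = 14: T = 35.6; 4.68, so 5 of 9
- L = 28: T = 49.6; 6.53, so 7 of 9
- L = 42: T = 63.6; 8.37, so 9 of 9

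Patients infused, of nine, for all detection days:

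| Found on | L = 1 | L = 7 | L = 14 | L = 28 | L = 42 |
|---|---|---|---|---|---|
| Day 6 | 2 | 3 | 4 | 6 | 8 |
| Day 14 | 3 | 4 | 5 | 7 | 9 |
| Day 30 | 6 | 6 | 7 | 9 | 9 |
| Day 42 | 7 | 8 | 9 | 9 | 9 |

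**Step 3: sensitivity to the accrual reading**

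Section 6.2 does not say whether the rate is per study or per site. At four per month at each of four sites, the gap is 30.4/16 = 1.9 days and the ninth infusion falls on day 15.2. A Day 14 finding then gives T = 1.9 + 14 + 1 = 16.9, so all nine are infused even with 24-hour reporting. Only Day 6 findings leave room: T = 8.9 gives 5 of 9, against 9 of 9 with a 14-day lag.

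**Step 4: how often the rule would be reached**

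The binomial chance of at least two DLTs in nine patients is 0.23, 0.56 and 0.80 at assumed DLT rates of 0.1, 0.2 and 0.3. In a simulation with detection equally likely on the four days and every DLT subject to the same lag, the chance that the second report arrives before the ninth infusion was as follows.

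| DLT rate | L = 1 | L = 14 | L = 28 | L = 42 |
|---|---|---|---|---|
| 0.2 | 0.30 | 0.16 | 0.05 | 0.005 |
| 0.3 | 0.52 | 0.31 | 0.11 | 0.01 |

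This overstates the real loss, because most DLTs in Step 1 would not take the slow route.

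**Step 5: need for a central count**

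With an assumed 3/2/2/2 split over four sites, there are C(9,2) = 36 patient pairs, of which 3 + 1 + 1 + 1 = 6 share a site. The other 30 (83%) do not.

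**The case against.** The strongest reply is that the gap is narrow. The protocol's dose target is bone marrow, and marrow toxicity is the kind that 9.1.3, 9.2 and 9.4.1 largely capture. Many Grade 3 non-haematological events would also be serious: 9.1.3 includes events needing intervention to prevent a serious outcome, and 9.4.1 describes Grade 3, for events outside the CTC list, as temporary disability requiring intervention. Monitoring frequency is tied to enrolment, so a long CRF lag is not a given. Putting both DLTs in patients 1 and 2 picks the case where delay matters most; at a 10% DLT rate it has probability 0.1 × 0.1 = 1%. All of this stands, and it limits the size of the point. It does not supply a deadline for the remaining class.

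Four stronger readings might be inferred, and the documents do not support them:
- *That DLTs at different sites defeat the rule by themselves.* Serious DLTs from every site go to one Medical Monitor within 24 hours.
- *That each investigator would see one DLT at most.* Under the 3/2/2/2 split, 6 of 36 pairs (17%) share a site.
- *That most patients would be infused before the stop.* This depends on the lag: a Day 6 finding with a 14-day lag gives 4 of 9.
- *That consented patients would be infused despite a stop.* Section 6.3 permits enrolment only when all criteria are met, including a pregnancy test within 24 hours of treatment where applicable, so a patient still in screening is ordinarily not yet enrolled. The wording of 10.2 is unclear on this, but not shown to be wrong.

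Nor is this matter for a statistical analysis plan: DLT reporting is safety conduct and belongs in the protocol.

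**Conclusion.** The concern holds for one class of event: a related, non-serious Grade 3 non-haematological DLT counts towards the stop, but no deadline brings it to the sponsor. The protocol's only numeric safety stop can therefore act late while everyone complies.

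In the illustration with DLTs found at Day 14, the delay costs 1, 2, 4 or 6 further infusions for lags of 7, 14, 28 or 42 days, relative to 24-hour reporting. These figures rest on study-wide accrual of four per month, both DLTs in the first two patients, and lags that are assumed. For DLTs first seen at Day 30 or 42, 6 or 7 of 9 patients are infused even with 24-hour reporting, because of the accrual pace; section 9.2 does not cause that part. Prompt reporting narrows the exposure without closing it.

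This should be fixed, but the narrowness of the class and the unknown lag do not support calling it critical.

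**What to change.** Amend 9.2 and 10.2 so that:
- every event meeting the 10.2 DLT definition, serious or not, is reported to the Medical Monitor on the SAE timeline;
- the Medical Monitor keeps the running cross-site DLT count and informs all sites of each DLT.

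The sponsor should also state in 10.2 whether stopping enrolment covers patients who have consented but have not yet been infused. This review does not choose that rule.

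The cost is a short amendment, a few extra 24-hour reports and a notice to sites for each DLT. No new assessment or visit is needed.

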### **Report all serious adverse events to:**

**Collectar Medical Monitor  
[name]  
[name]  
[contact]  
[contact]**

All SAEs will be evaluated by Collectar Medical Monitor. If the requirements for expedited reporting are met, Collectar will so report the adverse event to all regulatory authorities with jurisdiction over ongoing studies with the study drug, and to all other Investigators involved in clinical trials with the study drug. The Investigator must report all SAEs reported to regulatory authorities in an expedited manner to the local IRB.

## *9.3 DOCUMENTING ADVERSE EVENTS*

The Investigator should elicit information regarding the occurrence of adverse events through open-ended questioning of the patient, physical examination and review of laboratory results.

All adverse events, whether serious or not, will be described in the source documents and the adverse event page of the case report form. All new events, as well as those that worsen in intensity or frequency relative to baseline, that occur after administration of study drug through the period of protocol-specified follow-up must be captured.

Information to be reported in the description of each adverse event includes but not limited to:

- Medical diagnosis of the event (if a medical diagnosis cannot be determined, a description of each sign or symptom characterizing the event should be recorded)
- The date of onset of the event
- The date of resolution of the event
- Whether the event is serious or not
- Action taken:
  - None
  - Change in the study drug administration (e.g., temporary interruption in dosing)
  - Drug treatment required (specify)
  - Non-drug treatment required (specify)
  - Hospitalization or prolongation of hospitalization required (complete SAE page)
  - Diagnostic procedure performed (specify)
  - Patient discontinued from the study (complete final visit section of the CRF)
- Outcome:
  - Event resolved
  - Event resolved with sequelae
  - Event ongoing
  - Patient died (notify Collectar immediately, complete the SAE page and final visit section of the CRF)
- Patient condition is related or not related to the study drug
- Patient's condition is intermittent or continuing
- The grade of the event based on the NCI common toxicity criteria

